#### Imaging

PSMA PET-CT is performed according to institutional SOPs with locally available radiotracers. PET-CT imaging is performed at 3 centers using different PET-CT systems and protocols. In Wurzburg, scans are acquired on a Siemens Biograph mCT 64 or a Siemens Biograph mCT 128 Flow scanner. At 90 minutes after the injection of [¹⁸F]PSMA-1007 (3 MBq/kg body weight), patients undergo a whole-body PET acquisition with a scan duration of 2 minutes per bed position. In Augsburg, PET-CT scans are performed on a Siemens Biograph mCT 40 or a GE Discovery Molecular Imaging system. Patients receive approximately 4 MBq/kg body weight of [¹⁸F]rhPSMA-7.3 or [¹⁸F]DCFPyL (Pylarify), and imaging is conducted 60 minutes after injection with an acquisition time of 2 minutes per bed position. In Munich, PET scans are acquired on 2 hybrid PET-CT systems (Biograph molecular CT and Biograph Vision 600; Siemens). The radiotracer is predominantly [¹⁸F]rhPSMA-7.3, with [¹⁸F]PSMA-1007 used alternatively during cyclotron maintenance, and the injected activity is 3 MBq/kg body weight. Imaging is performed 60 minutes after injection for [¹⁸F]rhPSMA-7.3 and 90 minutes after injection for [¹⁸F]PSMA-1007, with an acquisition time of 3 to 4 minutes per bed position or a flow acquisition speed of 1.1 to 1.5 mm/s. In follow-up examinations, the administered radiotracer may differ from that used at baseline, depending on tracer availability and local clinical protocols. All scans are pseudonymized and transferred for central evaluation at Wurzburg. Response will be assessed by visual RECIP 1.0 relative to baseline after cycles 2, 4, and 6 by 1 reader. In case of a change of radiotracer during therapy, 2 readers in consensus will perform a visual assessment to minimize the potential effects of differences in visual PSMA-positive tumor volume, and the number of patients with a change in radiotracers will be stated in the final manuscript.

#### Clinical Data

Demographics, baseline tumor characteristics (Gleason score and metastatic sites), laboratory values (eg, PSA, lactate dehydrogenase, and alkaline phosphatase), and treatment details (ie, cycles administered and administered activity) are captured prospectively and pseudonymized before transfer to the central database for integration with ctDNA and imaging data.

### Data Management

All original source documents and records required for patient care during PSMA RLT are retained in the patients’ medical files at the respective treating hospitals. In accordance with the Radiation Protection Ordinance, these records are stored for a minimum of 30 years. LBx results are archived for 30 years at the Interdisciplinary Laboratory for Experimental Cancer Research. Clinical and laboratory data from the participating nuclear medicine departments (Wurzburg, Augsburg, and TUM Munich) are centrally combined in an electronic data capture master file at the University Hospital Wurzburg and made available to statistical collaboration partners for analysis. Pseudonymized PSMA PET-CT data are transferred in Digital Imaging and Communications in Medicine format to the Department of Nuclear Medicine, University Hospital Wurzburg, and stored together with the clinical and laboratory data for a period of 10 years. Written informed consent, including approval for pseudonymized data transfer among the collaborating centers, is obtained at each participating site and stored in the respective local study documentation. All study results are published in anonymized form in peer-reviewed journals, and anonymized research data may be made available to third parties upon reasonable request.

### Statistical Methods

The primary analyses evaluate the prognostic and predictive value of baseline ctDNA for treatment response after 2 cycles of PSMA RLT, as defined by imaging- and PSA-based criteria. Predictive performance is assessed using receiver operating characteristic analyses, including the determination of optimal ctDNA cutoffs, as well as sensitivity, specificity, positive and negative predictive values, and multivariable logistic regression models adjusting for relevant confounders.

Treatment response is further assessed by analyzing longitudinal changes in ctDNA levels and their concordance with PSMA PET-CT and PSA responses, using the Cohen κ coefficient and correlation analyses. Secondary analyses investigate associations between baseline and longitudinal ctDNA metrics and clinical or laboratory parameters, including subgroup comparisons based on patient characteristics. Exploratory analyses focus on the identification of very early molecular responders based on short-term ctDNA changes and on the characterization of clonal evolution and potential resistance mechanisms using deep sequencing and computational clonal deconvolution methods. General statistical considerations include the handling of missing data, adjustment for multiple testing, and sensitivity analyses to ensure robustness of the results. Given that tumor burden and ctDNA levels may change over relatively short time intervals in heavily pretreated mCRPC, the temporal separation between baseline PSMA PET-CT imaging and baseline blood sampling will be accounted for in the statistical analysis. The exact interval (in days) between PET-CT and blood draw will be recorded for all patients. The primary analysis correlating baseline ctDNA with PET-derived tumor burden will be prespecified to include only patients with a PET-to-blood interval of ≤28 days. In addition, sensitivity analyses will be performed in the full cohort, incorporating the PET-to-blood interval as a covariate (modeled as a continuous variable and as a categorical variable ≤28 vs 29‐56 days). Patients with intervals exceeding 28 days will be described separately, and the impact of their inclusion vs exclusion on key estimates will be explicitly reported. Furthermore, we will assess the association between cumulative administered activity and longitudinal changes of ctDNA. Cumulative activity will be modeled as a continuous exposure variable and analyzed in relation to ctDNA dynamics using regression-based approaches. Landmark analyses will be used where appropriate to mitigate immortal time bias.

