**Methods:**

LOOPS is a prospective, multicenter observational biomarker trial recruiting 100 patients with mCRPC eligible for PSMA RLT across 3 Bavarian cancer research centers in Germany. Patients will undergo up to 6 cycles of [^177^Lu]Lu-PSMA-617. Blood samples for ctDNA analysis will be collected longitudinally (at baseline and after cycles 1, 2, 4, and 6) and processed according to standardized protocols. Imaging with PSMA positron emission tomography–computed tomography and clinical and biochemical data will be systematically collected. The primary end points are the prognostic and predictive value of baseline ctDNA for treatment response, defined by imaging- and prostate-specific antigen (PSA)–based response criteria after 2 cycles of PSMA RLT. Predictive performance will be evaluated using receiver operating characteristic analyses, including the determination of optimal ctDNA cutoffs, sensitivity, specificity, positive and negative predictive values, and multivariable logistic regression models adjusting for relevant clinical confounders. Secondary end points assess the concordance and correlation between ctDNA dynamics, systematically assessed PSMA positron emission tomography–computed tomography response, and PSA changes, as well as associations between ctDNA and clinical or laboratory (eg, age, Gleason score, and other) characteristics at baseline and during follow-up. Exploratory analyses will investigate early molecular response patterns based on short-term ctDNA changes and will characterize clonal dynamics and potential resistance mechanisms under therapy.

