### Sample Size

The planned sample size of 100 patients is based on a priori biometrical considerations and reflects expected feasibility in this population with advanced mCRPC. Due to disease severity and anticipated attrition, the primary end point (treatment response at first posttherapy restaging after 2 cycles of therapy) is expected to be evaluable in approximately 70 patients. On the basis of this effective sample size, power calculations demonstrate that clinically meaningful differences in response rates between patients with and without a ctDNA-based predictive marker or marker change can be detected with 80% power at a 2-sided significance level of α=.05. Specifically, depending on the prevalence of the marker or marker change (25%, 50%, or 75%), differences in response probabilities of 0.33 to 0.41 between marker-positive and marker-negative patients are detectable using Fisher exact test. These effect sizes correspond to sensitivities ranging from 38% to 88% and specificities from 44% to 93%, supporting the ability of the study to evaluate the prognostic and predictive performance of ctDNA metrics. Therefore, the planned sample size is considered adequate for the primary analyses while remaining consistent with the pragmatic, multicenter, observational design of the study. To control the family-wise error rate for the 2 coprimary end points, a hierarchical testing strategy will be applied. The association between baseline ctDNA and treatment response will first be tested at a 2-sided significance level of α=.05. Only if this test is statistically significant, the discriminative performance (receiver operating characteristic analysis and area under the curve) will be formally evaluated at the same α level.

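### The baseline ctDNA cutoff is optimised by ROC and its accuracy reported in the same roughly 70 patients with no correction stated, and the form of ctDNA in the gatekeeping test is left open

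*Protocol article*

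**What the plan says.** Statistical Methods describes the primary analysis of baseline ctDNA against response after 2 cycles as "receiver operating characteristic analyses, including the determination of optimal ctDNA cutoffs, as well as sensitivity, specificity, positive and negative predictive values", together with multivariable logistic regression. The Abstract says the same: "including the determination of optimal ctDNA cutoffs, sensitivity, specificity, positive and negative predictive values".

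Sample Size states that the primary end point "is expected to be evaluable in approximately 70 patients". It claims that "differences in response probabilities of 0.33 to 0.41 between marker-positive and marker-negative patients are detectable using Fisher exact test", "with 80% power at a 2-sided significance level of α=.05", for marker prevalences of 25%, 50% and 75%, and translates these differences into sensitivities of 38% to 88% and specificities of 44% to 93%. The same section sets a hierarchy: the association of baseline ctDNA with response is tested first at .05, and ROC/AUC is formally evaluated only if that test succeeds.

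No numerical baseline cutoff appears anywhere. The Introduction lists the optimal threshold among the open questions. The only cutoff set in advance is the decline of at least 30% at 6 weeks (Outcomes), which is exploratory and concerns change, not baseline.

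**The concern.** A cutoff chosen because it separates responders from progressors best in one sample will look better in that sample than in new patients. Sensitivity, specificity and both predictive values read off at that cutoff inherit the bias. With about 70 patients the bias is not small, and these figures are part of the primary result, where readers will take them as estimates of how the marker performs.

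The second issue is the test that opens the hierarchy. The power statement rests on a two-group comparison with prevalence set in advance, yet the article does not say which form of baseline ctDNA the association test uses. A Fisher test keeps its level only when the grouping was made without looking at the outcome.

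**Working it through.** **Inputs.** From Sample Size: 70 evaluable patients, two-sided .05, 80% power, Fisher exact test, prevalence 25/50/75%. Assumed, because the article does not give them: the overall response rate, a normal marker on some scale, and the rule that picks the cutoff.

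**1. The plan's own figure.** Exact enumeration of Fisher power, solved for the smallest difference with at least 80% power, at an assumed overall response of 0.6:

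| Marker-positive / negative | Response rates | Detectable difference |
|---|---|---|
| 18 / 52 | 0.873 vs 0.505 | 0.368 |
| 35 / 35 | 0.775 vs 0.425 | 0.350 |
| 52 / 18 | 0.702 vs 0.307 | 0.395 |

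Across response rates of 0.3 to 0.7 the range is 0.325 to 0.40, so the stated 0.33 to 0.41 is reproduced to about 0.01.

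The accuracy range follows too. For 18/52, sensitivity = 18×0.873 / (18×0.873 + 52×0.505) = 15.7/42.0 = 0.37, and specificity = 52×0.495 / (52×0.495 + 18×0.127) = 25.7/28.0 = 0.92. The plan gives 38% and 93% as the extremes. The stated pairs back-solve to an overall response of about 0.58 to 0.59, so about 40% progression is a fair central setting. All of this assumes a grouping fixed in advance.

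**2. Optimism in the reported accuracy.** Simulate 70 patients. The marker is N(0,1) in non-progressors and N(d,1) in progressors, with d = √2·Φ⁻¹(AUC). Choose the cutoff c that maximises J = sensitivity + specificity − 1 in the sample. Compare the in-sample values with the true ones at that same c: sensitivity 1 − Φ(c − d), specificity Φ(c).

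- 40% progression: J is overstated by 0.124, 0.118 and 0.110 for AUC 0.65, 0.70 and 0.75. At AUC 0.70, apparent J is 0.38 and true J 0.26. Sensitivity is about 7 to 8 points too high and specificity about 4 to 5.
- Other settings:

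| Progression | Shift d | Apparent sens/spec | True sens/spec | Excess in J |
|---|---|---|---|---|
| 50% | 0.5 | 0.65/0.65 | 0.59/0.59 | 0.12 |
| 50% | 0.8 | 0.70/0.70 | 0.64/0.64 | 0.12 |
| 50% | 1.0 | 0.73/0.73 | 0.68/0.68 | 0.10 |
| 30% | 0.8 | 0.72/0.69 | 0.64/0.65 | 0.12 |

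A shift of 0.8 corresponds to AUC Φ(0.8/√2) = Φ(0.566) = 0.71. With no association at all, apparent 0.57/0.57 stands against a true 0.50/0.50. Progression is the positive class here; if response is, the two labels swap. The smaller outcome group takes the larger bias. A fresh run over 30% to 50% progression and AUC 0.65 to 0.75 confirmed about 4 to 9 points each.

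**3. Level of the association test under each reading.** No true association, n = 70, nominal .05:

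| Form of baseline ctDNA | Rejection rate |
|---|---|
| Continuous, rank test | 5.0–5.5% |
| Median split, Fisher | 2.4–2.9% |
| Youden cutoff within middle half of data, Fisher | 10% |
| Youden cutoff, direction fixed, Fisher | 14–15% |
| Minimum-p cutoff within middle half, Fisher | 20% |
| Youden cutoff, either direction, Fisher | 28–30% |
| Minimum-p cutoff, Fisher | 34–36% |

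**4. What a searched cutoff would cost in power.** To hold 5% after an unrestricted search, the nominal p must be about .014–.015 (Youden, direction fixed), .0065–.007 (either direction) or .005–.006 (minimum p). At nominal .006 to .01, power at the design differences falls from 80% to about 52–59%. This applies the stricter threshold at a fixed cutoff and is approximate.

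**The case against.** A reader might go further and infer that the gatekeeping test itself runs far above 5%. The article does not support that. Fisher's test is named only in the power calculation ("between marker-positive and marker-negative patients are detectable using Fisher exact test"). The gatekeeping test is described simply as an association, with no test and no dichotomy specified. It comes before ROC/AUC in the hierarchy, and the cutoff search sits inside the ROC analysis. Logistic regression, which can take ctDNA as continuous, is also listed. Nor is a ROC cutoff the only way to obtain two groups: ctDNA detected or not, or a genomic alteration present or not, are binary without any search. The prevalences of 25/50/75% are planning scenarios. All of this stands, so the inflation in step 3 is conditional.

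It is also fair that an article condenses the full plan, and that an analysis plan not shown may contain resampling or name the predictor. The Statistical Methods section promises adjustment for multiple testing and sensitivity analyses. The Discussion treats thresholds as candidates and asks for external validation before any clinical use.

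These points lower the stakes but do not remove the accuracy problem. The published text commits the primary analysis to choosing a cutoff and reporting its accuracy, and ties neither multiplicity adjustment nor validation to that step. Multiplicity adjustment cannot correct a biased sensitivity, and later validation by others does not correct the figures this study prints.

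**Conclusion.** The point holds in two parts of different strength.

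Firm: followed as written, the primary analysis yields sensitivity, specificity and predictive values that are too favourable. Sensitivity and specificity are overstated by about 4 to 9 points each and the Youden index by about 0.10 to 0.15. This rests on a normal marker, a Youden cutoff, 70 patients, 30% to 50% progression and AUC 0.65 to 0.75. It does not depend on which association test is run first.

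Conditional: the article leaves open which form of baseline ctDNA the gatekeeping test uses. If it is the ROC-derived cutoff, the type I error is about 10% to 36% depending on the search rule. If it is continuous ctDNA or a cutoff set without outcome data, it is about 5% or below. The stated power of 80% likewise applies only to a grouping fixed in advance.

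This should be corrected before the primary analysis, but it ranks below a defect that would invalidate the study: the study is observational, it claims no immediate clinical use, and the analysis plan may already settle part of it.

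**What to change.** 1. State what the gatekeeping test uses. One named continuous baseline ctDNA metric, tested by logistic likelihood-ratio or Mann-Whitney, is simplest. Alternatives are a cutoff fixed without outcome data, or, if a cutoff is searched, a permutation (maximally selected) p value, accepting the power loss in step 4 of the working.
2. Label any ROC-derived cutoff exploratory.
3. Report sensitivity, specificity, PPV and NPV with bootstrap optimism correction, re-selecting the cutoff in every resample, next to the uncorrected values.

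The cost is a short addition to the analysis plan and some code; no extra patients or samples are needed. The downside is less favourable reported accuracy. There is still time: recruitment is planned to finish in September 2026 and the primary publication is planned for mid-2027. Because ctDNA analysis began in January 2026, any fixed cutoff should be written down before ctDNA results are linked to response.

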### Eligibility Criteria

Adults (aged ≥18 years) with histologically confirmed prostate cancer that has progressed to mCRPC are eligible if they are candidates for PSMA RLT within approved indications, have previously received at least 1 androgen-receptor pathway inhibitor and 1 taxane-based chemotherapy, and have PSMA PET-CT within 8 weeks prior to cycle 1 demonstrating adequate target expression. Prior exposure to taxane-based chemotherapy is required as an inclusion criterion in accordance with regulatory approvals and the standard-of-care indication for PSMA-targeted RLT at the time of study design. This criterion ensures that all enrolled patients are treated within the approved clinical framework and reflects real-world treatment sequencing in mCRPC. Patients must provide written informed consent and must either be German speaking or have a translator available. Exclusion criteria are limited to the inability or unwillingness to adhere to study procedures and the absence of an interdisciplinary tumor board recommendation for PSMA RLT.

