### Outcomes

Two coprimary outcomes are specified. The first is the prognostic value of baseline ctDNA for nonprogression after 2 cycles, as assessed by PSA response according to PCWG3 (Prostate Cancer Clinical Trials Working Group 3) criteria [19]) and by RECIP 1.0 (Response Evaluation Criteria in PSMA-imaging, version 1.0) [20,21] defined as partial response or stable disease vs progression. The second is the concordance between ctDNA dynamics (percent change from baseline) and imaging-based response according to RECIP 1.0, as well as PSA response, after cycles 2, 4, and 6. Secondary outcomes examine associations between baseline ctDNA features and clinical or laboratory parameters (eg, age, Gleason score, PSA, alkaline phosphatase, lactate dehydrogenase, and metastatic distribution) and relate longitudinal ctDNA changes to clinical and laboratory trajectories. Exploratory outcomes include a very early molecular response defined a priori as a ≥30% decline in ctDNA at 6 weeks after the first cycle and the characterization of clonal dynamics and resistance-associated alterations across multiple time points.

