### Participant Timeline

Participants are enrolled before cycle 1. Blood sampling for ctDNA occurs at baseline (≤14 days prior to cycle 1); before cycle 2 (approximately 6 weeks); and at imaging visits after cycle 2 (approximately 16 weeks), cycle 4 (approximately 28 weeks), and cycle 6 (approximately 40 weeks). An exploratory time point at 6 weeks after the first cycle enables the assessment of very early molecular response. PSMA PET-CT is obtained at baseline and after cycles 2, 4, and 6 and submitted for central review (Figure 1). All patients are treated with the approved PSMA RLT according to the manufacturer’s recommendations; accordingly, the treatment schedule and administered activity are fixed.

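### The RECIP reference PET may be 56 days old at cycle 1, and the plan's 28-day interval control is not explicitly extended to the RECIP coprimary analyses

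*Protocol article*

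**What the plan says.** All places are in the Methods of the protocol article.

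- **Age of the baseline scan.** Under Eligibility Criteria, patients must "have PSMA PET-CT within 8 weeks prior to cycle 1 demonstrating adequate target expression".
- **Age of the baseline blood sample.** Participant Timeline: "Blood sampling for ctDNA occurs at baseline (≤14 days prior to cycle 1").
- **Role of the baseline scan.** Imaging: "Response will be assessed by visual RECIP 1.0 relative to baseline after cycles 2, 4, and 6 by 1 reader". The baseline PET is thus the reference for every RECIP reading.
- **Where RECIP enters.** Outcomes defines two coprimaries. "The first is the prognostic value of baseline ctDNA for nonprogression after 2 cycles, as assessed by PSA response" and also by RECIP 1.0. "The second is the concordance between ctDNA dynamics (percent change from baseline) and imaging-based response according to RECIP 1.0", and also PSA response.
- **Interval control.** Statistical Methods gives its reason, that burden and ctDNA may shift quickly in heavily pretreated disease. It then states: "The exact interval (in days) between PET-CT and blood draw will be recorded for all patients". The restriction follows: "The primary analysis correlating baseline ctDNA with PET-derived tumor burden will be prespecified to include only patients with a PET-to-blood interval of ≤28 days". Full-cohort sensitivity analyses use the PET-to-blood interval as a covariate, continuous and in two categories (up to 28 days, 29 to 56 days). The effect of including or excluding patients beyond 28 days is to be reported for key estimates, which are not listed.

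The correlation of baseline ctDNA with PET tumour burden is an objective in the Introduction, but Outcomes does not list it as a coprimary.

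**The concern.** A RECIP reading after cycle 2 compares the restaging scan with the baseline scan. Any growth between the baseline scan and the first dose is part of that change, although no radioligand had been given. The untreated time that matters here is PET to cycle 1. The plan records and models PET to blood, and names a restriction only for the cross-sectional correlation.

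Two consequences are possible:

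- **First coprimary.** If patients with high ctDNA also grow faster, they reach RECIP progression more often through growth before treatment. Part of the association of baseline ctDNA with progression after 2 cycles would then reflect growth before the first dose rather than failure on treatment.
- **Second coprimary.** RECIP change can include up to 8 weeks of untreated growth, while ctDNA change includes at most 2 weeks. The two measures then cover different periods, and κ falls for a reason unrelated to the biomarker.

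**Working it through.** **Windows, from the documents.** 8 weeks × 7 = 56 days, which agrees with the plan's upper category of 29 to 56 days. When PET precedes blood,

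PET-to-cycle-1 = PET-to-blood + blood-to-cycle-1.

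With PET-to-blood at most 28 and blood-to-cycle-1 at most 14, a patient who meets the rule can have a reference scan 28 + 14 = 42 days before cycle 1. A scan 29 to 42 days before cycle 1 falls in either category depending only on the blood-draw date.

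**Share of the RECIP interval that is untreated.** First restaging takes place "at imaging visits after cycle 2 (approximately 16 weeks"), which I count from cycle 1. The maximum share is:

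| Rule | Untreated / total | Share |
|---|---|---|
| None | 8 / (8 + 16) weeks | 33% |
| PET-to-blood ≤28 days | 6 / (6 + 16) weeks | 27% |
| PET-to-cycle-1 ≤28 days | 4 / (4 + 16) weeks | 20% |

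**How often the two rules disagree.** Assume PET age L is uniform on 0 to 56 days and blood age B uniform on 0 to 14 days.

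- P(PET-to-blood ≤28) = (28 + mean B)/56 = 35/56 = 62.5%.
- P(meets the rule but L >28) = mean B/56 = 7/56 = 12.5%.
- Ratio: 12.5/62.5 = 20% of those who meet the rule. Their mean PET age is 32.7 days, and none exceeds 42.

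**Untreated growth.** Growth = 2^(days/doubling time) − 1. The documents give no growth rate, so the doubling times are assumed.

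| Doubling time | 14 days | 56 days |
|---|---|---|
| 8 weeks | +19% | +100% |
| 12 weeks | +12% | +59% |
| 16 weeks | +9% | +41% |
| 26 weeks | +5% | +24% |

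**Effect on the estimates.** This is a simulation of 400,000 patients in which ctDNA has no relation to on-treatment change. Every input is assumed:

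- PET age uniform on 0 to 56 days.
- Growth rate lognormal (σ 0.5) around the stated doubling time, correlated 0.3 to 0.5 with ctDNA.
- Log on-treatment volume change N(−0.15, 0.6).
- Progression at 1.2 times the reference volume or more.
- ctDNA change equal to on-treatment change plus N(0, 0.3).

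Results over doubling times of 26 to 8 weeks:

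| Quantity | No untreated growth | Full cohort | PET ≤28 days before cycle 1 |
|---|---|---|---|
| Progression | 29% | 36% to 53% | – |
| AUC of baseline ctDNA | 0.50 | 0.51 to 0.56 | 0.51 to 0.54 |
| κ, ctDNA change vs RECIP | 0.69 | 0.67 to 0.49 | 0.69 to about 0.63 |

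**Would a covariate do instead?** Adding PET-to-cycle-1 days as a main effect to the logistic model moves the spurious ctDNA odds ratio from 1.23 to 1.25 (8-week doubling, correlation 0.5) and leaves it at 1.09 (26-week doubling). PET age is independent of ctDNA in this model, so it is not a confounder. The bias comes from growth rate multiplied by PET age, and a main effect does not remove that.

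**The case against.** The strongest reply has five parts.

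1. **The text does not exclude the coprimaries.** Statistical Methods says the temporal separation will be accounted for and promises results with and without long intervals for key estimates. These may include the coprimaries. A reader might infer that the interval control covers neither coprimary; the wording is ambiguous and does not establish that. The ambiguity stands, and the promise would in any case use PET-to-blood.
2. **PET-to-blood is not simply the wrong interval.** It is right for the correlation to which it is attached. It differs from PET-to-cycle-1 by at most 14 days when PET precedes blood, and under uniform timing the two correlate at 0.97. In the simulation, restricting on one or the other changes the null AUC by at most about 0.007. This stands in full.
3. **The size is assumed and may be small.** The AUC shift of 0.01 to 0.06 compares with a null standard error of √(71/(12 × 35 × 35)) = 0.07 for 70 patients split evenly. The RECIP reading is visual, so a sharp volume threshold may not represent it. This stands, and it limits the claim to a possible bias.
4. **Scope.** The PSA components do not depend on the PET date. The first coprimary is prognostic, so ctDNA that marks fast-growing disease is partly what it seeks. That tempers the AUC point. It does not answer the κ point, where the two measures cover different periods.
5. **This is detail for an analysis plan.** An article may leave covariates to a fuller document. Here, however, the article itself fixes the interval, the cutoff, the categories and the analysis, so what it attaches them to is open to comment.

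**Conclusion.** The point holds in a limited form. The two baselines can differ in age by several weeks, the plan accepts that this can matter, and it names its restriction for an analysis that is not a coprimary. Growth before the first dose can be counted as RECIP progression, which may slightly inflate the apparent association of baseline ctDNA with RECIP outcome and lower κ.

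It would go too far to say that pre-treatment growth will be read as progression on treatment. The documents give no growth rate, no distribution of PET ages and no volume threshold for the visual reading. The figures above show a range under assumptions: close to nothing at 26-week doubling (κ 0.69 to 0.67), and material at 8-week doubling (κ 0.69 to 0.49). This is a worthwhile, inexpensive addition to the analysis and does not invalidate the design.

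**What to change.** - Derive PET-to-cycle-1 days from the scan and first-treatment dates, and report the distribution.
- Prespecify that both RECIP coprimary analyses (baseline ctDNA against nonprogression, and κ between ctDNA change and RECIP) are repeated in patients with PET at most 28 days before cycle 1, and reported beside the full-cohort result.
- State which key estimates are covered by the comparison with and without long intervals.
- Keep PET-to-blood for the cross-sectional correlation of ctDNA with tumour burden.
- Do not rely on PET-to-cycle-1 as a main-effect covariate, since it does not remove this bias.

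The cost is one derived variable and a few sentences, with no new scans or patients and no change to the clinical imaging window. The downside is precision: under uniform PET timing the subset is 28/56 = 50%, about 35 of the roughly 70 evaluable patients. It also removes the bias only in part; in the worst simulated case κ recovers to about 0.63, not 0.69. With restaging after cycle 2 running to the end of 2026 and publication planned for mid-2027, this can still be fixed before the primary analysis.
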